## Synopsis of the clinical investigation

The purpose of this post market study is to demonstrate the clinical improvement due to the use of a powered extension assist knee ankle foot orthosis, or EA-KAFO, in individuals with knee extension deficiency due to cerebral palsy (CP) in a domiciliary setting. The EA-KAFO tested in this investigation, whose commercial name is Agilik™, is registered as a Class 1 medical device in the EU MDR and with the US FDA (Food and Drugs Administration, USA). The design of the study is schematized in Figure 1.

[figure not shown]

Figure 1: study design

## Device information

### Device identification

Agilik™

### Device description

#### Design

The fabricated knee-ankle-foot orthosis (KAFO) is individually developed for each patient. For this reason, the illustrations in the Instruction for Use attached to the protocol ("D0476-04\_IFU AGILIK MVP Lite) only show one possible (KAFO) that has been fitted with the "Agilik."

#### Function

The Agilik is a powered orthosis system that can assist or resist motion independently in each gait phase. It is normally used as a pair of joint orthoses, one for each leg. The device can apply up to 12 Nm across the knee joint in the direction of either flexion or extension. The system consists of an orthosis for each leg, a battery, a carry pack, cabling and application software running on a computer. The orthosis itself consists of an electro-mechanical actuator with integrated electronics that is attached as a lateral hinge on a conventional, patient-specific custom-molded KAFO. A foot pressure sensor is embedded in the footbed of the KAFO and connected to the actuator.

The foot sensor and angular velocity are used to detect the gait phase of the patient and communicate with the motor controller to provide a unique torque for each gait phase. The torque ramp and intensity can be modified through the Agilik App to cater towards individual patients by assisting or resisting motion during their gait. This allows for the clinician working with the patient to adjust the settings of the device for the patient's needs.

#### Classification

The Agilik is classified as a Class 1 medical device. According to IEC 60601-1 the Agilik system is classified as a body-worn INTERNALLY POWERED MEDICAL EQUIPMENT rated for NON-CONTINUOUS OPERATION. The normal duty cycle of the device is regular use for one full charge of the battery, and then recharging the battery (~3.5 hours) before use of the device again.

#### Applied Parts

- Battery pack
- KAFO shell and straps

No other applied parts or parts subject to the requirements of applied parts are identified through the risk management process.

#### Enclosures

Any enclosures rated for protection against ingress of fluid and particulate matter are marked accordingly using IPXX format on the equipment. See the Instruction for Use attached to this protocol (D0476-18\_IFU AGILIK 1.1) for a description of relevant markings.

### Intended purpose of the device and target population

The product is intended for orthotic fittings of the lower limbs. The product is intended for patients with lower extremity weakness resulting in gait pathology such as, but not limited to crouch gait from

a diagnosis of cerebral palsy, muscular dystrophy, spina bifida, or incomplete spinal cord injury or post stroke hemiparesis.

#### Conditions of Use:

- The product is intended for forward walking on flat, dry ground. Adult supervision is required for children.
- It is the responsibility of the therapist/clinician to determine if the patient is physically and cognitively able to understand and use the product.
- If the patient is dependent upon existing patient support systems like crutches or walkers, it is recommended to continue use of them alongside the Agilik. Any walker used with the Agilik must be adjusted wide enough to accommodate the KAFO plus actuator width.
- The product can be used for home and community mobility at the discretion of the clinician considering the ability of the patient to use the device. In this case, the patient and family must be trained by a Bionic Power certified individual.
- The product must not be used for other activities including, but not limited to, running, jumping, squatting, and ascending or descending stairs/ramps. If the patient needs to do any movement or enter any terrain not intended for use with the Agilik, the device should be powered down or removed.
- The product must only be used with the correct customised KAFO developed by an authorised orthotist for each specific patient with the patients' shoes worn on the outside of the KAFO.
- Fitting of a patient with the product and KAFO may only be carried out by a Bionic Power certified clinician.
- The product is intended exclusively for multiple use by a single patient. Use of the product by more than one patient is not approved by the manufacturer.

#### Traceability

The Agilik orthosis used during the investigation will bear a label to uniquely identify them, including a serial number.

#### Materials coming into contact with the human body

The Agilik is a robotic knee hinge integrated in a custom KAFO; the Agilik itself is not in direct contact with the skin or with the human body. For further information, see the Instruction for Use attached to the protocol (D0476-18\_IFU AGILIK 1.1).

#### Medical or surgical procedures involved in its use

Adequately trained healthcare personnel will make patients wear and use the orthosis.

#### Necessary training and experience for the use of the device

#### Training and Qualification of the O&P Professional

The fitting of a patient KAFO shell with the product may only be carried out by certified O&P professionals who have been authorised with the corresponding Bionic Power training.

### **Training and Qualifications of the Therapist or Nursing Staff**

Certified physical therapists and nursing staff may only handle and operate the product after being trained. Training must be carried out by Bionic Power Inc. authorised personnel.

### **Background literature review**

Cerebral palsy (CP) is the most common motor disorder affecting children . Among CP, spastic diplegia is very prevalent and occurs in more than 50% of the total CP population . The motor deficits in spastic diplegia typically produce a walking pattern, termed crouch gait, which is characterized by exaggerated stance phase knee flexion, and may be accompanied by increased hip adduction and internal rotation, and a plantarflexed, neutral, or dorsiflexed ankle . The majority of children with spastic diplegia eventually walk; however, this is often delayed and the walking patterns they develop differ from normal pediatric gait . Even though CP is not considered a “progressive” disorder from a neurological standpoint, it has been reported that approximately 50% of those with CP who are ambulating as adolescents will cease to do so in early or middle adulthood due to worsening musculoskeletal deformities such as crouch gait , along with the secondary effects of reduced physical activity such as decreased strength and endurance.

There are multiple potential contributors to crouch gait, including muscle spasticity, contracture, poor selective motor control, dystonia, muscle imbalance, and muscle weakness. These symptoms can occur in muscles crossing the ankle, knee, and/or hip joints and involvement at any one or more of these joints may precipitate crouch. The relative contribution of each of these factors may vary across patients. The only potentially effective treatment when crouch gait is caused by muscle contracture is orthopedic surgery to increase muscle-tendon length. These procedures must be done advisably because muscles could become over-lengthened or weakened further leading to an exacerbation of crouch rather than correction. Surgical outcomes have therefore been shown to be variable, but are purportedly better if the surgery is based on results from an instrumented gait analysis evaluation, simultaneous multi-level correction is performed when it is evident that multiple joints are involved, and procedures shown to cause excessive weakness are avoided.

Anti-gravity (extensor) muscle weakness in CP may not be the precipitating factor in crouch gait in the majority of cases, but clearly contributes as greater deterioration in crouch gait is observed with increasing age in part because the increase in muscle strength does not keep pace with the rate of body growth . The major muscle groups that provide antigravity lower limb extension are the hip extensors, knee extensors, and ankle plantar flexors, all of which have been shown to be weak in children with CP . Achieving and maintaining adequate strength levels in those with motor disabilities is challenging. Traditional ankle bracing compensates for weakness or spasticity by providing passive support or blocking unwanted motions , respectively, and often leads to greater weakness in these muscles over time. Clearly there is a need for more effective training strategies or devices that can preserve or possibly even augment strength on a continuous basis for those with CP, and thereby help to maintain gait function.

In order to improve crouch gait in children with CP, the Bionic Power Inc. has developed and commercialised Agilik™, whose effectiveness has already been demonstrated in a small sample of patients with CP (the device is CE-marked and FDA-approved). Therefore, the goal of this investigation is to demonstrate the clinical improvement due to the use of the device in home setting through a randomised study stratified according to gender and GMFCS.

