### **General Information of the protocol**

The clinical investigation will be a study with the following characteristics:

- Confirmatory and Not first-in-human;
- Randomised controlled study;
- Prospective study;
- Multicentric.

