### **Endpoints and measured variables**

In order to demonstrate the clinical improvement due to the use of the device, we will consider the following primary endpoints:

- Distance walked during a 6-minutes walking test (6MWT);
- The KEMS measured during gait analysis assessment

---

 Enright, Paul L. "The six-minute walk test." Respiratory care 48.8 (2003): 783-785

In addition, secondary endpoints will be considered with the following purposes:

- at T0 (baseline), T1 (post intervention) and at T2 (follow-up)
  - Measurements of the Joint ROM and muscle lengths
  - To determine the level of spasticity in the lower limbs with the Modified Ashworth scale (MAS)
  - To assess postural and motor abilities with Gross Motor Function Measure-88 (GMFM-88)
  - To assess functional gait assessment (walking speed) with the 10-meter walking test (10mWT)
  - To evaluate kinematics and kinetics assessments (gait pattern) with the 3D gait analysis overground with EMG data acquisition
  - To determinate self-perception of performance in everyday living with Canadian Occupational Performance Measure (COPM)
  - To quantify static balance with Centre of Pressure (COP) detection using the force platforms of the gait analysis lab when available
- at T1 only in the Intervention Group:
  - to assess the usability and acceptability of Agilik in parents/caregivers with the System Usability Scale (SUS) and the Technology Acceptance Method 3 (TAM-3)
  - to investigate aspects of behavioural engagement during the use of the Agilik device at home with semi-structured interviews with patients and their families

Only parents/caregivers of participants in the intervention group will be provided with a diary to freely explore, during the training, their thoughts and feelings about the device, in order to have a more extensive monitoring of the treatment.

Finally, an exploratory outcome will be:

- to perform a remote monitoring of gait behavior with sensorized shoes by Magnes (MAGNES AG, [name]). If possible, during the months between T0 and T1 we will ask the participants of both groups to wear the shoes during indoor and outdoor walking, allowing us to acquire gait data to assess spatiotemporal parameters during daily life.

---

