### Information on the investigational device, on any comparator and on any other device or medication to be used in the clinical investigation

During the investigation, different sets of Agilik devices will be used for each of the six clinical experimental centres. They will be uniquely identified through labels reporting their serial numbers. No other devices will be tested. For other information on Agilik, refer to the section “*Device description*”.

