### Information on subjects

We will enroll 40 children with knee extension deficiency due to CP according to sample size calculation.

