#### Inclusion criteria:

- Volunteer who have a diagnosis of CP and a crouch gait
- Provision of signed and dated informed consent form.
- Stated willingness to comply with all study procedures and availability for the duration of the study, or alternatively, ability to do so based on parent report and physician observation during history and physical examination.
- Age between 5 and 17
- body weight between 20 and 125 Kg
- Knee flexion retraction assessed in supine position by less than 10°. Hamstring contracture as assessed by straight leg raising test does not limit ability to participate in the study.
- Subjects must not have had a tibio-tarsal arthrodesis. In addition, they must have at least 5° of passive dorsi-flexion of the ankle.
- Able to walk at least 3 m without stopping, with or without a walking aid.
- Able to understand and follow simple directions based on parent report and physician observation during historical and physical examination.
- GMFCS level I, II and III
- MAS score  $\leq 2$

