### Procedures

This is a study of subjects with CP to demonstrate the clinical improvement due to the use of Agilik in children with knee extension deficiency due to cerebral palsy (see Figure 1 in section *Synopsis of the clinical investigation*). Participants will be enrolled based on inclusion and exclusion criteria and medical/physical history. Included children will be randomly divided into two groups (hereafter Intervention and Control Groups), stratified according to GMFM and gender, for a randomised control study. Both groups will start signing the informed consent.

The first visit is for physical examination and T0 assessments, which will include:

- 6MWT and KEMS measured during gait analysis, for demonstrating the clinical improvement due to the use of the device
- GMFM for postural and motor assessment
- 10mWT for functional gait assessment
- MAS to evaluate the level of spasticity in the lower limbs
- Joint ROM and muscle lengths examination performed manually by a medically responsible individual
- 3D gait analysis overground with EMG
- COPM for self-perceived performance assessment
- COP detection to quantify static balance.

Then, the Control Group will continue with standard therapy and daily life activities, and we will ask the participants to wear the sensorized shoes by Magnes during their outside walking when possible.

On the other hand, the Intervention group will start the intervention, which consists of:

1. 3 visits dedicated to exoskeleton preparation at the orthopedic center (casting for brace fabrication, set-up and calibration of the system).
2. Training with Agilik (4-5 weeks, 2 sessions/week) during which patients will practice walking with the device. Also the families will be trained to be able to autonomously use the system during home rehabilitation.
3. Home rehabilitation (2 months, 30 minutes/day, 5 days/week) during which subjects will practice walking with the device at home. Moreover, we will ask the participants to wear the sensorized shoes by Magnes during their outside walking when possible. Furthermore, children/parents will be asked to fill a diary to assess engagement in using this device.

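### Centre is not among the randomisation factors, although 40 children are spread over six centres, so arms will often be lopsided within a centre

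*Protocol*

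**What the plan says.** The protocol (General Information of the protocol) calls the trial "Multicentric", and the section on the investigational device says that "different sets of Agilik devices will be used for each of the six clinical experimental centres". Information on subjects sets the size: "We will enroll 40 children with knee extension deficiency due to CP according to sample size calculation". No target per centre is given.

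The randomisation factors are stated twice. The Background literature review has "through a randomised study stratified according to gender and GMFCS". Procedures has "stratified according to GMFM and gender, for a randomised control study". The two disagree on the functional factor, GMFCS in one and GMFM in the other. They agree in leaving centre out.

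The section on minimising bias relies on randomisation, standardised procedures and calibrated equipment, and does not mention centre. Statistical considerations plans comparisons with T0 within groups and a comparison between groups. The method is to be chosen by normality; no model or covariates are named.

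**The concern.** Centre can matter here in ways that act after T0. The control arm continues standard therapy, whose content is not defined and may differ between centres. The intervention arm has 4 to 5 weeks of supervised training, and clinicians adjust the torque settings for each child. KEMS comes from gait analysis performed at several sites.

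With about 7 children per centre, balance on gender and gross motor function gives no balance within a centre. A centre whose children fall mostly in one arm says little about the device effect, and its own level enters the difference between arms. Allocation factors are settled before the first child is randomised, so an analysis plan written later can adjust for the resulting imbalance but cannot prevent it.

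**Working it through.** **Inputs from the protocol.** 40 children, six centres, two groups with 18 per group required. Gender has 2 levels and the inclusion criteria admit "GMFCS level I, II and III", so 2 × 3 = 6 strata. Effect sizes are 0.4 (6MWT) and 1.0 (KEMS), correlation 0.5, significance level 0.025, power 0.80, dropout 10%.

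**Assumptions not in the protocol.** Centres of 7, 7, 7, 7, 6 and 6 (mean 40/6 = 6.7); permuted blocks of 4 within six near-equal strata; centre share of variance s of 5%, 10% or 20% in the quantity analysed.

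**1. The plan's sample size.** Power for at least one endpoint is 1 − P(Z1 < c − 0.4√(n/2), Z2 < c − 1.0√(n/2)) with correlation 0.5. At n = 18, √(18/2) = 3, so the shifts are 1.2 and 3.0.
- c = 1.96 (one-sided 0.025 per endpoint): power 85.7% at n = 18; n = 16 suffices.
- c = 2.24 (two-sided 0.025 per endpoint): power 78.2% at n = 18; n = 19 is needed.

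The stated 18 lies between these, and 36/(1 − 0.10) = 40. The calculation has no term for centre.

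**2. How often centres are lopsided** (simulation)

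| Event in at least one centre | Blocks in six strata | 20:20 without strata |
|---|---|---|
| 5:2 or worse (5:1 or worse in a centre of 6) | 91% | 89% |
| 0 or 1 child in an arm | 54% | 52% |
| All children in one arm | 8% | 7% |

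The columns barely differ: the stated factors do nothing for balance within centres.

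**3. Size of the chance shift.** Let a_j and b_j be the proportions of the two arms that come from centre j. With total SD 1, centre adds to the difference between arms a component with variance s × Σ(a_j − b_j)². The simulated mean of that sum is about 0.086.
- s = 5%: √(0.05 × 0.086) = 0.066
- s = 10%: √(0.10 × 0.086) = 0.093
- s = 20%: √(0.20 × 0.086) = 0.131

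**4. Precision recovered for KEMS.** Two-sided 0.025, 18 per arm, noncentral t with noncentrality 3.0/√(1 − s). Degrees of freedom are 34 unadjusted and 34 − 5 = 29 with centre in the model. Centres are taken as balanced between arms.

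| | Power |
|---|---|
| Unadjusted | 0.741 |
| Adjusted, s = 0 | 0.735 |
| Adjusted, s = 5% | 0.759 |
| Adjusted, s = 10% | 0.783 |
| Adjusted, s = 20% | 0.833 |

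For the plan's at-least-one rule with c = 2.24, 78.2% becomes 80.4%, 82.6% or 87.1% (lost degrees of freedom ignored). If the assumed effects are instead on the within-centre SD, leaving centre out lowers 78.2% to 76.0%, 73.5% or 68.0%.

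**5. The alternatives.** Crossing centre with gender and GMFCS gives 6 × 6 = 36 cells for 40 children, or 40/36 = 1.1 per cell, so stratified blocks would fail. Minimisation on the three factors, giving the better-balancing arm with probability 0.80, lowers the 54% to about 10% when squared imbalances are summed. It is about 16% with absolute imbalances and about 5% if centre has double weight.

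**The case against.** **The analysis is not fixed.** A reader might infer that the plan leaves centre out of the analysis. The document does not support that. It names no model, and covariates are commonly left to an analysis plan, which is not shown here. This objection stands. The point concerns the allocation factors; the power figures show what a centre term could recover, not a loss to which the plan is committed.

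**There is no bias on average.** A reader might also infer that lopsided centres would create a false device effect. Randomisation keeps the comparison unbiased over repetitions. The shift of 0.07 to 0.13 is small beside the sampling error of a standardised difference, √(2/18) = 0.33, and beside the assumed KEMS effect of 1.0. Where total SD is used, it is already part of that sampling error. This stands too; the cost is precision, and possible confounding in the one trial that is run.

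**Comparison with T0 helps.** Stable differences in level, such as a laboratory offset, would largely cancel in change scores or with T0 adjustment. Differences in control therapy, training or device tuning arise after T0 and would not. The objection stands in part, and it argues for the lower end of the assumed range.

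**Few factors are reasonable in a small trial.** This is true of stratified blocks, given 36 cells. It does not hold against minimisation.

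**Some centre differences are inferred.** Procedures places device preparation at an orthopaedic centre, so fitting at each of the six sites is not established. The wording "To quantify static balance with Centre of Pressure (COP) detection using the force platforms of the gait analysis lab when available" concerns a secondary endpoint and does not show that KEMS or 6MWT is measured differently between sites. Standardised procedures, calibration and manufacturer-authorised training should limit variation. These limits stand, and the true centre share of variance is unknown.

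**Conclusion.** The point holds as one about allocation. Both statements of the randomisation factors omit centre. Under the assumed centre sizes and blocks, about 54% of randomisations leave at least one centre with 0 or 1 child in an arm, and 7 to 8% put a whole centre in one arm. Unequal recruitment would change these figures. The consequence is modest: a chance shift with SD of about 0.07, 0.09 or 0.13 for assumed centre shares of 5%, 10% or 20%, and forgone KEMS power of about 0.02 to 0.09. It is worth acting on before allocation starts, because the sample size has little margin (78.2% to 85.7% by reading of the significance level) and the remedy needs no more children. The documents support neither a claim of systematic bias nor a claim that centre is excluded from the analysis.

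**What to change.** In the Background literature review and in Procedures, state one set of factors, settling whether gross motor function enters as GMFCS level or as GMFM. GMFCS has three defined levels; no cut points are given for GMFM.

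Allocate centrally by minimisation on centre, GMFCS level and gender, with a random element (for example probability 0.80 for the better-balancing arm). State the imbalance score and the weights, since they move the remaining chance of a lopsided centre between about 5% and 16%.

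In Statistical considerations, say that the balancing factors, including centre, are carried into the between-group comparison of KEMS and 6MWT. Centre can be a random intercept, or a fixed effect if that model does not converge, with the T0 value as a covariate.

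The cost is a change to the randomisation set-up and the added model terms. Allocation becomes slightly more predictable in an open trial, which the random element and central allocation limit. If centres do not differ, the five centre degrees of freedom lower KEMS power only from 0.741 to 0.735.
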